### Health economics analysis plan

The health economics modelling will address the following three questions: (1) What is the cost-effectiveness of a new screening pathway for diabetes and prediabetes? The screening approaches will comprise: diabetes risk score followed by definitive laboratory tests; diagnostic model which the statistical modelling finds to be more accurate than diabetes risk score followed by definitive laboratory tests; RBG for all without diabetes risk score based prescreen; HbA1c test with no prescreen and; no screening; (2) What is the cost effectiveness of a new screening pathway for DR among people with diabetes? The screening approaches will comprise a new method, which the statistical modelling finds to be accurate; retinal photographs only and no screening and (3) What is the cost effectiveness of a new screening pathway for a range of other complications of diabetes among people with diabetes? The screening approaches will comprise a new method, which the statistical modelling finds to be accurate; a combination of HbA1c, lipids and urine tests and colour retinal images; and no screening. In each case, therefore, one comparator will be a ‘gold standard’ (HbA1c test, retinal photographs and combination of tests as above) and another will be no screening and no treatment until symptoms of DR, DKD or other complications of diabetes are experienced.

The modelling will draw on the following data sources: (1) the data collected through the house-to-house screening and associated retinal images, blood and urine tests on the rates of true and false positives and negatives, the characteristics of people with diabetes and its complications, and their quality of life; (2) the data collected through the study on the cost per person of this screening and its cost per person with diabetes, and the costs of clinic visits and treatments for DR; (3) the data and information from past studies on the incidence rates by age and gender of diabetes, DR and other complications of diabetes, transition rates between different stages of the disease and disease-specific mortality rates; and (4) the data from past studies on the costs of care for people with varying severities of DR and other complications of diabetes and on their quality of life. For those variables on which data cannot be collected in this study or obtained from past studies, expert views will be sought, and sensitivity analyses conducted.

The modelling will comprise development of Markov models to track people aged 40 years and above (a) through incidence of diabetes, any DR, STDR, severe visual impairment/blindness and (b) through incidence of diabetes, mild complications other than DR and severe complications other than DR. For each disease state, the models will contain estimates of average annual costs of care and average EQ-5D quality of life. The design of the models will be developed in the light of data availability.

The models will be used to estimate lifetime costs and quality of life (monetised quality adjusted life years, QALYs) from age 40 years and above (a) where the planned screening approach (or approaches) is conducted and necessary treatment given shortly after screening; (b) where the ‘gold standard’ screening approach is conducted and necessary treatment given shortly after screening; and (c) where no screening is conducted and no treatment given until symptoms develop. The incremental cost effectiveness of the screening in comparison with ‘gold standard’ screening will be estimated by comparing (a) and (b); and its incremental cost effectiveness in comparison with no screening will be estimated by comparing (a) and (c). A wide range of sensitivity analysis will be conducted, and a variety of discount rates may be applied.

We will also evaluate and compare the cost effectiveness of retinal photography for everyone with diabetes versus retinal photography only for people with diabetes with suspected high risk of DR, to be developed through the statistical modelling. We will develop a health economics plan after reviewing available data. As an example, Rachapelle *et al*^31^ used a WHO-recommended approach for a cost-effectiveness threshold in their study of the cost utility of telemedicine to screen for DR in India. Under that approach, the interventions costing less than per capita gross domestic product (GDP) per QALY were considered very cost effective, interventions between one time and three times GDP were considered cost effective and interventions more than three times GDP were not considered cost effective.

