## Abstract

**Introduction:**

The aim of this study is to develop practical and affordable models to (a) diagnose people with diabetes and prediabetes and (b) identify those at risk of diabetes complications so that these models can be applied to the population in low-income and middle-income countries (LMIC) where laboratory tests are unaffordable.

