Due to the large numbers of undiagnosed diabetes, it is also useful to investigate whether it is more efficient to triage people at risk of diabetes in the population using non-invasive diabetes risk scores, such as Madras Diabetes Research Foundation-Indian Diabetes Risk Score (MDRF-IDRS)^18^ to further reduce the cost of screening with POC HbA1c or RBG.

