### Objectives

Our study has three important objectives. The first objective is to determine the ideal tests that could identify people at risk of diabetes and prediabetes in community screening that can be applied to LMIC. In order to accomplish this, we would evaluate the correlation of RBG levels with POC HbA1c levels and decide on a cut-off value for RBG from HbA1c to diagnose prediabetes. Second, we will evaluate whether initial triaging with NL diabetes risk score followed by either RBG or POC HbA1c only to the identified risk group is more effective than screening everyone for diabetes using either RBG or POC HbA1c. Third, we will develop affordable, easily deliverable and clinically effective model to accurately identify people at risk of complications of diabetes in community screening, especially DR.

Secondary objectives are aimed at guiding future policies on screening of diabetes and its complications. As the study involves a large sample and the setting up of a teleophthalmology model to screen for DR across 20 regions in India, we will be able to report the regional prevalence of DR and the associated risk factors, the inter-grader reliability and the accuracy of using artificial intelligence to grade DR. We will also conduct economic modelling and process evaluation of a holistic model for screening of all complications of diabetes. If sample size permits, we will be able to report on region-specific and diverse population-specific rates of diabetes and complications, visual impairment, quality of life and risk models specific to regions to inform local health authorities.

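### The economic strategy list for diabetes screening omits both triaged strategies of the second objective; its only risk-score arm ends in a laboratory test, so triage is not cleanly isolated

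*Protocol article*

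**What the plan says.** **Objectives.** The second of the three main objectives concerns triage. Its triaged side is worded as "initial triaging with NL diabetes risk score followed by either RBG or POC HbA1c only to the identified risk group". The comparator is one of the same two field tests given to all participants without a prior score. That is four strategies: two triaged, two untriaged.

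**Introduction, Screening for people at risk of diabetes.** The reason given for triage is economic: "to further reduce the cost of screening with POC HbA1c or RBG".

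**Health economics analysis plan, question 1.** The approaches open with "diabetes risk score followed by definitive laboratory tests; diagnostic model which the statistical modelling finds to be more accurate" and end with "RBG for all without diabetes risk score based prescreen; HbA1c test with no prescreen and; no screening". The gold standard comparators for the three economic questions are listed as "HbA1c test, retinal photographs and combination of tests as above", so for diabetes it is the HbA1c test, with no assay named.

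**Health economics analysis plan, comparisons.** A planned approach (a) is compared with the gold standard (b), and "its incremental cost effectiveness in comparison with no screening will be estimated by comparing (a) and (c".

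**Study procedures.** Glycaemia is measured by capillary RBG and by a POC HbA1c kit. No laboratory glucose or HbA1c test is described. The Abstract places the target population "in low-income and middle-income countries (LMIC) where laboratory tests are unaffordable".

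**The concern.** To learn what triage is worth, two arms must share the same test and differ only in whether the risk score comes first. The second objective is framed that way. The economic list is not: its risk-score arm changes the test as well.

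A difference in cost or QALYs between that arm and an untriaged field-test arm could come from triage, from the laboratory test, or from both. The laboratory step is also one for which this study collects neither cost nor accuracy, and one that the intended users are said not to be able to pay for. What is at stake is whether the economic model can say if a risk score in front of the study's own tests saves money, which is the reason the protocol article gives for considering triage.

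**Working it through.** The protocol article gives no figure on this point, so there is none to reproduce. The check sets the two lists side by side and then writes out what the mismatch does to cost.

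**Step 1. Strategies compared.**

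| Strategy | Second objective | Economic question 1 |
|---|---|---|
| Risk score, then RBG | yes | no |
| Risk score, then POC HbA1c | yes | no |
| RBG for everyone | yes | yes |
| POC HbA1c for everyone | yes | HbA1c without prescreening, assay not labelled |
| Risk score, then laboratory tests | no | yes |
| More accurate diagnostic model | no | yes |
| No screening | no | yes |

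Two of the objective's four strategies are absent from the economic list.

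**Step 2. Is there a pair that differs only in triage?**

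- Risk score then laboratory tests against RBG for all: triage and test both change. This is certain from the text.
- Risk score then laboratory tests against HbA1c without prescreening: if that HbA1c is the study's POC kit, both change. If it and the laboratory step are the same laboratory HbA1c, the pair isolates triage, but for a test that the second objective does not name.
- No pair isolates triage for RBG or, on the face of the text, for POC HbA1c.

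**Step 3. Effect on test cost per person screened.** Let s be the cost of the risk score, f the share referred, c the cost of the field test and L the cost of the laboratory test.

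- Triage effect with the same test: s + f·c − c
- Contrast available from the list: s + f·L − c
- Difference, due only to the change of test: f·(L − c)

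The protocol article gives none of these values. As an assumption, take s = 0, f from 0.4 to 0.6 and L/c from 0.5 to 3.

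- Triage effect: 0.4c − c = −0.6c, to 0.6c − c = −0.4c. Always a saving.
- Listed contrast, lowest: 0.4 × 0.5c − c = −0.8c. Highest: 0.6 × 3c − c = +0.8c.

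The listed contrast can therefore show a loss where triage itself saves. With s = 0 this happens once L/c exceeds 1/f, that is 2.5 at f = 0.4 and about 1.7 at f = 0.6. True and false positive rates are mixed in the same way.

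**Step 4. What the study can supply.** The risk score and RBG are collected on all participants, so f can be observed. POC HbA1c is taken only in known diabetes, in RBG ≥160 mg/dL, and in 50 participants per cluster at 110–159 mg/dL. With 20 regions × 3 clusters = 60 clusters, that last group is 60 × 50 = 3,000 people of at least 48,000. Nobody without known diabetes and with RBG below 110 mg/dL is selected for HbA1c.

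**The case against.** **The accuracy analysis can answer the second objective.** That objective asks about effectiveness, and economic modelling is placed under the secondary objectives. Statistical considerations plans sensitivity, specificity, predictive values and combinations of tests. This stands. A reader might infer that the second objective goes unanswered; the text does not support that. What lacks its matching arms is the cost side, which the Introduction gives as the reason for triage.

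**A health economics plan is still to be written.** True, and it could add the arms. But the article already states which approaches the comparison will comprise, and that list disagrees with its own objective. This is a contradiction between two stated lists, not a detail left for later.

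**The strategies are compared with each other.** A reader might infer from the comparisons with gold standard and no screening that competing strategies never meet. That goes too far. HbA1c is the gold standard for diabetes, so RBG for all against HbA1c is a planned (a) versus (b) contrast, and for retinopathy the plan adds photography for everyone against photography for those at high risk. What stands is narrower: no direct comparison is stated between two approaches neither of which is the gold standard, so even if score then RBG were added, its contrast with RBG for all would not follow from the stated scheme.

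**The laboratory step can be modelled from outside data.** The plan allows past studies or expert views with sensitivity analyses. This stands for feasibility, but it does not make the arm comparable with the field-test arms.

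**The diagnostic-model entry can be read two ways**: as a model followed by laboratory tests, or as a model more accurate than score plus laboratory tests. This stands, so only one laboratory arm, the risk-score one, is certain.

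**Conclusion.** The point holds as an inconsistency to be reconciled. Two of the four strategies in the second objective are absent from economic question 1, and the only risk-score arm ends in a test outside the study's procedures. The confounding of triage with test is certain against RBG for all. Against HbA1c without prescreening it is conditional on reading that arm as the POC kit, which the Objectives and Study procedures suggest but the economic plan does not state.

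The numerical range in the working rests entirely on assumed costs and referral shares. It shows that the sign can reverse, not that it will. Sample size, power and error rates are unaffected. The correction is worth making before the health economics plan is written.

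**What to change.** 1. Add risk score then RBG, and risk score then POC HbA1c, to economic question 1.
2. Label the HbA1c arm as POC or laboratory, and do the same for the gold standard.
3. State a direct comparison of each triaged arm with the untriaged arm that uses the same test: score then RBG against RBG for all, and score then POC HbA1c against POC HbA1c for all. Keep the comparisons with gold standard and no screening.
4. Keep laboratory confirmation as a scenario.
5. State that HbA1c accuracy is only partly observed. Use sampling weights for the 110–159 mg/dL group, which requires that the 50 per cluster be drawn at random or by a known rule. Use outside inputs with sensitivity analysis for people without known diabetes and with RBG below 110 mg/dL. The same gap affects the false-negative rate of any arm judged against HbA1c.

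The cost is a revision to the strategy list and a few more model runs. No added field data are needed.

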**Trial registration number:**

ISRCTN57962668 V1.0 24/09/2018.

Strengths and limitations of the studyThis is the first national prospective study that will assess the prevalence of sight-threatening diabetic retinopathy (DR) in various regions in India.The study will provide evidence on the accuracy of point-of-care glycated haemoglobin as a screening tool for diabetes.The study will provide several diagnostic models on diabetes and its complications.Validation of the models may not be possible in all cases.The treatment pathway for patients identified with sight-threatening DR or other complications of diabetes is according to local protocols.

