BP will be recorded in sitting position in the right arm to the nearest 1 mm Hg using the electronic OMRON machine (Omron Corporation, Kyoto, Japan). Participants with BP ≥140/90 mm Hg and not on antihypertensive drugs will be advised to contact a physician for further evaluation. A simple finger-prick test will be used to assess capillary RBG using a standard POC testing device (OneTouch Verio Glucometer, LifeScan Inc, USA). All participants with known diabetes or those with capillary RBG ≥160 mg/dL and 50 participants with RBG 110–159 mg/dL in each cluster will receive further tests. These include HbA1c estimation using a POC kit (A1c Now Plus, PTS Diagnostics, USA) and POC lipid estimation (Cardiochek PA analyser, PTS Diagnostics, USA). A POC urine sample (Chemstrip Micral dipstick, Roche Diagnostics, Mannheim) will be tested for the presence or absence of microalbuminuria.

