Visual acuity in both eyes will be recorded using a tablet/smartphone-based vision check web-based application (Peek Vision). Non-mydriatic fundus photography of both eyes will be done using a handheld retinal camera (Visuscout 100, Zeiss, Germany). This portable and battery-operated camera with in-built Wi-Fi facilities will allow capture of colour and red-free retinal images covering 40° field of view through pupils as small as 3.5 mm. Two fundus images (one macula-centred and one disc-centred) of each eye will be captured. In case of any media opacities making fundus imaging difficult, the anterior segment image of each eye would be taken. A teleophthalmology system will be set up whereby the images captured by each fieldworker will be uploaded to a cloud-based study specific database and graded at the local clinical centre by an ophthalmologist/optometrist (primary grader), as well as transferred to four central reading centres, where grading will be done by a second ophthalmologist (secondary grader). Discrepancies between primary and secondary grading will result in arbitration by a senior retinal consultant. Any participants with STDR, ungradable images and other incidental findings requiring further evaluation will be informed by the fieldworkers and counselled to attend hospital eyecare service. DR will be classified as per the International Clinical Disease Severity Scale for DR as no DR, mild/moderate/severe non-proliferative DR (NPDR) and proliferative DR (PDR).^23^ Diabetic macular oedema (DMO) will be determined as present or absent. STDR would be defined as the presence of severe NPDR, PDR and/or DMO. Artificial intelligence may be applied to grade these images and if found to be as accurate as human graders, it will be incorporated to the screening model.

The well-established and widely used quality of life questionnaire EQ-5D (Euro Quality of life) will also be administered with additional vision ‘bolt-on’ questions and vision-related quality of life.^24–26^ The study flow is shown in figure 2. In addition, centre administrators at each clinical site will be responsible for contacting, by letter or phone, and tracking follow-up of those participants who need further referral to an eye hospital for treatment for STDR or due to ungradable retinal images.

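### The economic model's screening scenarios assume that everyone found to need treatment gets it promptly, which understates the cost per QALY of screening against no screening

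*Protocol article*

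**What the plan says.** The Health economics analysis plan names three scenarios for lifetime costs and QALYs.

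- Scenario (a), the planned approach, is the case "where the planned screening approach (or approaches) is conducted and necessary treatment given shortly after screening".
- Scenario (b), the gold standard, carries the same assumption: "screening approach is conducted and necessary treatment given shortly after screening; and (c) where no screening is conducted".
- Scenario (c) is the case "where no screening is conducted and no treatment given until symptoms develop".

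The planned comparisons are (a) with (b) and (a) with (c). The plan also compares retinal photography for all people with diabetes with photography only for those thought to be at high risk of retinopathy.

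Other sections describe what happens after a positive finding.

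- Study procedures: participants with STDR, ungradable images or other findings needing evaluation "will be informed by the fieldworkers and counselled to attend hospital eyecare service".
- Study procedures: participants with raised blood pressure who are not on treatment for it "will be advised to contact a physician for further evaluation".
- Study procedures: centre administrators contact eye referrals by letter or phone and are responsible for "tracking follow-up of those participants who need further referral to an eye hospital for treatment for STDR or due to ungradable retinal images".
- Strengths and limitations list, printed under the trial registration number: "The treatment pathway for patients identified with sight-threatening DR or other complications of diabetes is according to local protocols".

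The four data sources listed for the model cover test accuracy, participant characteristics, quality of life, costs (including clinic visits and treatment for retinopathy), incidence, transition and mortality rates. Attendance after referral and treatment uptake are not among them.

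**The concern.** Screening is paid for in everyone screened, but the health gain arises only in those who attend and are treated. If the model lets treatment follow detection in all who need it, it credits screening with gains that a programme based on referral may not deliver. Scenario (c) gets no corresponding benefit.

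The study's own description makes full and prompt uptake an unlikely base case. Referral depends on the person acting on advice, and the special-category clusters deliberately include groups with poor access to care or a low tendency to seek it. The study expects to track what happens to eye referrals, so it will hold information on this step that the model is not said to use.

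Cost-effective diagnostic models are a listed secondary outcome, and the stated purpose is to guide screening policy. An optimistic base case against no screening would carry straight into that advice.

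**Working it through.** **The plan's own figures.** The article states no cost per QALY and no attendance rate, so there is no economic figure to reproduce. The expected case count does reproduce: 0.30 × 4800 + 0.15 × 4800 = 2160 with retinopathy, and an implied 10% of these gives 216 with STDR. It is used below only to set a prevalence.

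**Screening against no screening.** Let S be the screening cost per person found to need treatment, T the net treatment cost and Q the QALY gain in a person treated, and u the proportion of those found who are treated. Non-attenders follow the course of scenario (c).

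- Cost per QALY at uptake u: (S + uT)/(uQ) = S/(uQ) + T/Q.
- At u = 1: (S + T)/Q.
- With f = S/(S + T), the ratio of the first to the second is f/u + (1 − f).

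For positive S and T this exceeds 1 whenever u is below 1. Neither f nor u is in the documents, so both are assumed over a range:

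| Screening-cost share f | u = 80% | u = 50% | u = 30% |
|---|---|---|---|
| 25% | 1.06 | 1.25 | 1.58 |
| 50% | 1.125 | 1.50 | 2.17 |
| 75% | 1.19 | 1.75 | 2.75 |

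Example cell: f = 50%, u = 50% gives 0.50/0.50 + 0.50 = 1.50. Delay before treatment is not included in these multiples.

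**One screening strategy against another.** All inputs here are assumed except the case count and the 9600 people with diabetes (4800 known plus 4800 new). The new method has 85% sensitivity at a cost of 6 per person. The gold standard has 100% sensitivity at a cost of 10. Treatment costs 100 and gains 1 QALY per treated case.

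- Extra screening cost of the gold standard: 9600 × (10 − 6) = 38,400.
- Extra cases treated: 216 × 0.15 × u = 32.4u.
- Extra cost per QALY: 38,400/(32.4u) + 100.
- At u = 100%: 1185 + 100 = 1285. At u = 50%: 2370 + 100 = 2470.

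Full uptake thus makes the gold standard's extra cost per QALY look about half of what it is at 50% uptake. The same reasoning applies to photographing everyone with diabetes against photographing only those at high risk: the more sensitive and more costly option is flattered.

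**The case against.** The strongest reply is that this is a journal summary. It says that a health economics plan will follow and that model design will depend on the data available. It promises a wide range of sensitivity analyses, and expert views where data are lacking. It plans a process evaluation covering reach, adoption and implementation. The phrase about prompt treatment may be meant only to contrast the screening scenarios with treatment at symptoms. No sentence states 100% uptake.

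Part of this stands: the later plan could bring uptake in. But none of this text names uptake, and sensitivity analyses would leave the stated base case as it is. The article defines the scenarios in words that leave no room for non-attendance, so this is a stated rule and not merely an omitted detail.

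Some stronger readings are tempting, but the documents do not support them.

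- A reader might infer that every screen-positive person is treated. The text speaks of necessary treatment, and false positives are a separate model input.
- A reader might infer that referral is by advice alone. Eye referrals also get letter or phone contact.
- A reader might infer that the study can supply uptake throughout. The tracking described covers STDR and ungradable images only, not newly detected diabetes, blood pressure or other complications. Attendance under study reminders may also exceed routine attendance.

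**Conclusion.** The point holds for scenarios (a) and (b) against (c): followed as written, the model understates the cost per QALY whenever screening has a cost and uptake is below 100%. The size is illustrative, at 1.25 to 1.75 times the full-uptake value for an assumed uptake of 50% and screening-cost share of 25% to 75%.

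It would be wrong to conclude that the assumption favours the new screening approach throughout. In (a) against (b) both sides share it, and the benefit goes to the more sensitive strategy where that one costs more. This could count against the affordable method that the study sets out to develop.

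Nor can one say that a result would cross a GDP-based threshold. The article cites that threshold only as an example and gives no starting cost per QALY. Likewise, the 216 expected STDR cases are a sample-size expectation. The model follows a lifetime cohort, so they cannot be turned into a count of people wrongly credited with treatment.

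**What to change.** In the Health economics analysis plan, redefine the base case of (a) and (b) so that treatment is received by the proportion who attend and start it, with the delay observed, and let non-attenders follow the course of (c).

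- For eye referrals, take attendance and delay from the tracking described under Study procedures, noting that study reminders may raise attendance above routine levels.
- For newly detected diabetes and other complications, use past studies or expert ranges.
- Add uptake and delay to the listed data sources and vary them in sensitivity analysis.
- Keep full, prompt uptake as a named best-case scenario.

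The health economics plan is still to be written, so the cost is wording, the added model parameters and extraction of the tracked referral data. The downsides are less favourable results against no screening and some inputs from outside the study.

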### Outcomes

The primary outcome is the correlation of RBG levels and POC HbA1c levels. Secondary outcomes include the cut-off value of RBG to define prediabetes; diagnostic accuracy of risk stratification models for diabetes; prevalence and risk stratification for screening for DR; risk model for those at risk of complications of diabetes; identification of cost-effective diagnostic model for diabetes, prediabetes and complications of diabetes and process evaluation of minimally invasive community screening for diabetes and its complications.

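### For question 1 of the economic evaluation, the stated pairwise ratios do not compare the three candidate strategies with one another, and the plan does not say how a saving per QALY lost will be read

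*Protocol article*

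**What the plan says.** All of this is in the protocol article. In the Health economics analysis plan, question 1 (diabetes and prediabetes) names first "diabetes risk score followed by definitive laboratory tests; diagnostic model which the statistical modelling finds to be more accurate than diabetes risk score", the latter also tied to definitive laboratory tests, and then "RBG for all without diabetes risk score based prescreen; HbA1c test with no prescreen and; no screening". HbA1c is the gold standard for this question and no screening is the second fixed comparator, which leaves three candidates.

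Lifetime costs and monetised QALYs are to be estimated for (a) "where the planned screening approach (or approaches) is conducted and necessary treatment given shortly after screening", (b) the gold standard and (c) no screening. Incremental cost effectiveness is then defined by two pairs only: against gold-standard "screening will be estimated by comparing (a) and (b); and its incremental cost effectiveness in comparison with no screening" by setting (a) against (c).

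Questions 2 and 3 have one new method each, plus gold standard and no screening. The section also plans one direct comparison of retinal photography for everyone with diabetes against photography for those at high risk. It promises a later health economics plan and, as an example from an earlier study, describes bands in which "the interventions costing less than per capita gross domestic product (GDP) per QALY were considered very cost effective", one to three times GDP was cost effective, and more than three times was not.

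The Outcomes section lists "identification of cost-effective diagnostic model for diabetes, prediabetes and complications of diabetes" among the secondary outcomes.

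**The concern.** Choosing one of several mutually exclusive strategies requires knowing what each step up in cost buys over the next cheaper option worth considering. A ratio against no screening averages over all the steps below it, so several strategies can look acceptable together even when the extra QALYs of one over another are very expensive.

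The comparison with the gold standard has a different problem. The study seeks affordable substitutes, so a candidate may well cost less and yield fewer QALYs than HbA1c for all. Both differences are then negative and the ratio is money saved per QALY given up. A high value is favourable and a low value unfavourable, the reverse of the usual reading. The text does not say how such a ratio will be interpreted, and the only bands it mentions are written for the usual direction.

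At stake is which screening approach for diabetes and prediabetes is reported as the cost-effective one.

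**Working it through.** **Step 1: pairs stated.** Five strategies give 5 × 4 / 2 = 10 pairs. Three candidates against two fixed comparators give 3 × 2 = 6. The other four are the three pairs between candidates, and gold standard against no screening. This counts RBG for all as a type (a) approach. If it were not one, only 2 × 2 = 4 pairs would be stated and RBG for all would appear in none of them. Questions 2 and 3 have three strategies and 2 of 3 pairs stated; if the new method lies between the other two in cost and effect, those two pairs are the steps that a full incremental analysis needs.

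**Step 2: illustration for question 1.** The article gives no costs, QALYs or GDP figure. All values here are assumptions, per person, with cost in units of per capita GDP. Ratio = cost difference / QALY difference.

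| Strategy | Cost | QALYs | v no screening | v HbA1c for all |
|---|---|---|---|---|
| No screening | 0 | 0 | | |
| Risk score, then laboratory tests | 0.010 | 0.020 | 0.010/0.020 = 0.50 | 0.070/0.010 = 7.00 |
| RBG for all | 0.022 | 0.022 | 0.022/0.022 = 1.00 | 0.058/0.008 = 7.25 |
| Diagnostic model, then laboratory tests | 0.030 | 0.0235 | 0.030/0.0235 = 1.28 | 0.050/0.0065 = 7.69 |
| HbA1c for all | 0.080 | 0.030 | not a stated pair | |

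Against no screening, all three candidates are well below 3 × GDP. The steps between them are:
- risk score to RBG: 0.012/0.002 = 6.0
- RBG to model: 0.008/0.0015 = 5.33
- risk score to model directly: 0.020/0.0035 = 5.71
- model to HbA1c: 0.050/0.0065 = 7.69

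The step to RBG (6.0) costs more per QALY than the next step to the model (5.33), so RBG is extendedly dominated. None of this shows in the stated pairs against no screening.

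**Step 3: net monetary benefit**, value per QALY (λ, in GDP) × QALYs − cost:
- λ = 1: score 0.010, RBG 0, model −0.0065, HbA1c −0.050
- λ = 3: score 0.050, RBG 0.044, model 0.0405, HbA1c 0.010
- λ = 6: score 0.110, RBG 0.110, model 0.111, HbA1c 0.100
- λ = 15: score 0.290, RBG 0.308, model 0.3225, HbA1c 0.370

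The best strategy changes from score to model to HbA1c as λ rises. Picking the lowest ratio against no screening would choose the risk score at every λ.

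**Step 4: direction of (a) against (b).** In the table, ratios of 7.00 to 7.69 would be labelled not cost effective under the example bands, although at λ = 3 all three candidates have higher net benefit than HbA1c (0.050, 0.044 and 0.0405 against 0.010). Two simple cases show the reversal:
- Saving 0.05 for 0.01 QALY lost: ratio 5. Net benefit −0.01 + 0.05 = +0.04 at λ = 1, and −0.03 + 0.05 = +0.02 at λ = 3. Favourable, but outside the bands.
- Saving 0.005 for 0.01 QALY lost: ratio 0.5. Net benefit −0.01 + 0.005 = −0.005 at λ = 1, and −0.03 + 0.005 = −0.025 at λ = 3. Unfavourable, but in the best band.

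**Step 5: can a weak test pass both stated comparisons?** Assume a gold standard at (0.018, 0.013), a good candidate A at (0.004, 0.010) and a weak candidate W at (0.002, 0.003). W is 0.002/0.003 = 0.67 against none and 0.016/0.010 = 1.6 against gold, inside 3 × GDP both times. A is 0.004/0.010 = 0.40 and 0.014/0.003 = 4.7, outside it once. Net benefit favours A: 0.006 against 0.001 at λ = 1, and 0.026 against 0.007 at λ = 3.

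**The case against.** The strongest reply is that details are left to a health economics plan not yet written, and that ranking, dominance and net benefit normally belong there. That would answer an omission. Here, however, the article already states which pairs will define incremental cost effectiveness, and for question 1 that choice is incomplete.

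Several other replies stand and limit the point:
- A reader might infer that results will be judged by the GDP bands. The text reports them as an example from an earlier study and adopts no threshold, so the reversal is a risk if such a ceiling is carried over, not a planned error.
- A reader might infer that the stated outputs cannot identify the best strategy. Costs and QALYs are estimated for each approach, so differences between candidates follow by subtraction, and monetised QALYs allow a net-benefit ranking once a value per QALY is set. The ratios alone do not give this.
- A reader might infer that a test detecting nobody could be declared cost effective. Against no screening it adds cost and no QALYs, so the stated (a) against (c) comparison would show it as dominated. The weak test in step 5 is the harder case.
- It would be too strong to say that rival approaches are never compared. The photography comparison is direct, and the second objective sets triage against screening everyone, though on effectiveness and not on cost per QALY.
- It is not certain that a candidate loses QALYs against the gold standard. Two candidates end in definitive laboratory tests. The reversal applies only where a candidate is both cheaper and less effective.

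**Conclusion.** The concern holds for question 1. The stated ratios cover 6 of 10 pairs, include none between the three candidates, and so do not by themselves deliver the secondary outcome of identifying the cost-effective model. In the illustration, candidates at 0.50 to 1.28 × GDP per QALY against no screening are separated by steps of 5.7 to 6.0 × GDP from the cheapest. For questions 2 and 3 the two stated pairs largely suffice, provided that they are read in the right direction.

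The reading of (a) against (b) is open for all three questions wherever the new method is cheaper and less effective. The article does not support saying that a GDP threshold will be misapplied, or that the best strategy cannot be recovered from the model's outputs. The numerical sizes rest wholly on assumed costs and QALYs; the count of pairs and the direction of the reversal do not.

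**What to change.** In the Health economics analysis plan, for question 1, replace the two pairwise ratios by a full incremental analysis of all five strategies: rank by cost, remove dominated and extendedly dominated strategies, and compare each remaining one with the next cheaper. Equivalently, rank all five by net monetary benefit over a stated range of values per QALY, which suits the intention to monetise QALYs.

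For all three questions, add that a ratio for a cheaper, less effective strategy will be read as a saving per QALY lost, or by net benefit, and not against a cost-per-QALY ceiling.

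The cost is a few lines of wording and a little more analysis of the same model outputs, with no new data. Fewer strategies may end up labelled cost effective.
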